### Intervention

Several theories have been postulated on how change in healthcare can be accomplished, and how effective change strategies can work in implementation of innovation. In cognitive theories, professional behaviour is considered to result from rational processes and experiences from earlier caseloads. In social interaction theories, change of professional behaviour is thought to be strongly mediated by peers in a group, the strength of inter-individual ties within groups, the existence of opinion leaders, and how much the desired behaviour is consistent with, and fits in, everyday practice. In total quality management theories, the use of systematically gathered data is considered to be crucial to facilitate effective professional development. These data can then be used in plan-do-study-act cycles (PDSA cycles) to provide insight into displayed behaviour and help identify areas where improvement is possible. This leads to the description of targets. These theories may overlap or may be complementary. In implementation science, the use of these theories as a framework is considered obligatory [32]. This intervention therefore will be multifaceted and consist of audit, comparative graphical feedback, and small group work with peer review of each other's performance, discussion of barriers to change, reaching agreement on future policy, and testing the agreement. After randomization to arm A or B, each group can choose from the corresponding set of five clinical topics allocated to that arm, to decide which three topics they want to discuss. Two balanced sets of topics, one for each arm, have been defined by the researchers. Each set consists of three major topics, from which the group has to choose two, and two minor topics, one of which has to be chosen. Thus, each LQIC will be asked to complete the entire strategy for three clinical topics of their choice during the intervention period. They are free to schedule extra meetings on topics not included in this trial, but these meetings will not be included in the final analysis. Feedback on the topic under discussion will be sent to the medical coordinator (diagnostic feedback) or local community pharmacists (prescription feedback) two weeks prior to the test ordering or the prescribing session of the LQIC, together with the relevant educational materials (see under 'clinical topics'). The first session, which will last approximately 90 minutes, will address the diagnostic test ordering behaviour of the individual GPs and will have the structure described under 'session structure' (Table 2). During this session, the GPs will discuss their diagnostic test ordering patterns and relate them to the guidelines provided. Individual and group working agreements will be created after barriers to change have been discussed. The second session will have the same structure, but the subject for discussion will be physicians' prescribing performance. This session will end by creating group and individual working agreements about preferred medication. Barriers to change from an individual perspective will again have to be discussed. After this first topic has been completed, the cycle will be repeated, for a new topic, as shown in Table 3. At the start of this new cycle, the group will reflect on the previous agreements, and revise them if necessary. The working agreements will then be prepared for further dissemination in the practices. Each session will be chaired by a member of the LQIC itself. When test ordering is discussed, a local representative from the diagnostic centre will be present, while a local community pharmacist will be present when pharmacotherapy is discussed. They will act as moderators, not as chairpersons.

**Table 2 T2:** Session structure

90 minutes	5 min	Explaining the method/reflection on previous topic
	
	5 min	Critical look at participants' own feedback
	
	5 min	Pairwise/group discussion on inter-individual differences
	
	25 min	Plenary discussion, relating feedback to guidelines
	
	10 min	Pairwise discussion on barriers to change
	
	25 min	Plenary discussion on barriers to change, aimed at problem solving
	
	15 min	Drawing up individual and group working agreements

**Table 3 T3:** Example of a schedule for the intervention

Topic	GPs	Medical coordinator	Community pharmacist
1. Anaemia	1. Meeting on tests	Moderator	Prepares second session
	
	2. Meeting on drugs	Prepares third session	moderator

2. Chlamydia infections	3. session on test and drugs (anaemia) 1. session on tests (Chlamydia)	moderator	Present as expert

We will test the model and the logistics needed prior to the large-scale implementation. We plan to do this in a small pilot study involving five groups of GPs. This pilot study will run for four months, during which period the participating GP groups will schedule two meetings. Each session will be structured according to the method provided by the researchers. The first session will address test ordering, while the second session will address prescribing. For reasons of efficiency, a set of only three topics will be used for the pilot study. The topics, which have been proposed by the project team members, are anaemia, dyspepsia, and asthma in combination with chronic obstructive pulmonary disease (COPD).

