##### Effect

1. Do the volumes of tests ordered and drugs prescribed change in the preferred direction, as described in the working agreements of the LQICs, compared to baseline?

2. What is the effect of this strategy on GPs' test ordering and prescribing behaviour in terms of interphysician variation and total volumes of tests and prescriptions with respect to specific clinical topics, compared to that among GPs exposed to the same strategy but for other topics?

3. Is any gain in the level of group performance predictive of the effect achieved?

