#### Effect evaluation

1. The volumes of particular tests ordered and particular drugs prescribed for which the group has agreed that change, either decrease or increase, would be necessary.

2. The total volumes of tests ordered and drugs prescribed by the participating GPs for the clinical topics chosen.

3. The inter-physician variation in test ordering and prescribing behaviour for the clinical topics chosen.

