### Measurements

Prior to randomization, the chair of the group will be asked to fill out a short pre-randomization form, with which we will be able to determine the number of GPs in the group and be able to assess the level of group performance [See Additional file 1]. Data on test ordering and prescribing behavior will be extracted from the existing databases at baseline (t = 0) and t = 6 months, t = 12 months and t = 18 months. The dataset obtained at t = 0 and the final set will be used for a before-after analysis. A new questionnaire will be sent to the chair, assessing the level of group performance after the intervention. After each meeting, the chair will be asked to fill out a form with questions about the structure of the session, whether working agreements were created, whether barriers to change were discussed and if so what the nature of these barriers was, what educational materials were used, and the group members' experiences with the strategy.

The process of implementing the strategy in the south of the Netherlands will be monitored. Participants will be questioned about their experiences with the strategy. Participating GPs will be asked to report their experiences with the strategy, and to provide us with the necessary details on the sessions they have attended. After each session, the targets set by each group will be recorded.

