### Time schedule

The intervention period will start in September 2007 and run through the spring of 2009. Process evaluation will start when all groups are included. During the intervention, new datasets will be obtained every six months in order to keep the databases up-to-date for future use in new sessions.

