## Discussion

To our knowledge, few studies have been published on the transfer of effective implementation strategies to the field. Our strategy has proved to be effective in an earlier trial on test ordering by GPs in the Netherlands. However, because this strategy was disseminated and controlled by academics, it remains unclear how large its effect will be when transferred to the field. We set up a pragmatic design in order to test this final step in implementation research, giving the diagnostic centres a leading role and leaving GPs much room to adapt and to internalise the strategy. The project team will act as facilitators to these centres, the pharmacists involved, and the LQICs. The strategy is targeted first on test ordering and second on prescribing, which is the natural order followed by GPs when consulted by a patient.

Our strategy is based upon several theories on effective behaviour change and on effective implementation. These theories can be identified at several levels of organisation in our trial. At the level of diagnostic centres and the LQICs, we expect the innovators and early adopters to join the trial, which refers to Roger's innovation-diffusion theory [34]. Within groups we expect to see change according to theories such as Ajzen's theory of planned behaviour and the PDSA-cycles [25,35]. During a meeting, we expect to see the preparation for change based on performance data and actual actions towards change. When new data will be provided to the groups, we expect reflection on the goals previously set. The theory of planned behaviour states that individuals are willing to show change in behaviour dependent on the perceived control over the behaviour itself, the attitude of the individual to the desired behaviour, and the perceived social norms. By providing graphical comparative feedback, we target at these perceived social norms. Comparative feedback sets the norm for a group, and through the phenomenon that one does not like to be an outlier we expect regression to the mean with regard to the inter-physician variation. The moderator who is also an expert on the subject under discussion is expected to act as opinion leader. Furthermore, even a GP from within the group itself can act as a local opinion leader and thus influence the rest of the group.

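### Effect outcome 1 is defined by working agreements that groups may revise during follow-up, so its items and their direction can come to depend on follow-up results

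*Protocol article*

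**What the plan says.** In the protocol article, Effect evaluation, outcome 1 is defined as "The volumes of particular tests ordered and particular drugs prescribed for which the group has agreed that change, either decrease or increase, would be necessary". The first effect research question takes the sign of success from the same source. It asks whether volumes "change in the preferred direction, as described in the working agreements of the LQICs, compared to baseline".

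The Intervention section describes what happens to an agreement once a topic is finished and the next begins: "At the start of this new cycle, the group will reflect on the previous agreements, and revise them if necessary". It gives no criterion for when a revision is needed. Table 3 shows the earlier topic returning, for both tests and drugs, in the session that opens the next topic.

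On data flow, Measurements has volumes extracted "at baseline (t = 0) and t = 6 months, t = 12 months and t = 18 months", and the first and last of these datasets form the before-after analysis. Time schedule adds: "During the intervention, new datasets will be obtained every six months in order to keep the databases up-to-date for future use in new sessions". The Discussion says: "When new data will be provided to the groups, we expect reflection on the goals previously set".

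On record keeping, Measurements states: "After each session, the targets set by each group will be recorded".

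**The concern.** An outcome should be fixed before the data that will be used to judge it are seen by anyone who can change it. Here the participants set the list of items and the desired direction, they know which intervention they are receiving, and they may reset both partway through. If a reset follows feedback on the same volumes, the outcome is partly selected on its own interim values.

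This is separate from two other features of outcome 1: targets may be chosen because they are extreme at baseline, and question 1 is put against baseline rather than against the other arm. Selection on follow-up would remain if both of those were dealt with.

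At stake is the answer to effect question 1. If poorly performing targets were withdrawn or had their direction reversed, a strategy with no effect would appear to move targets the agreed way. If targets already met were retired and the unmet ones kept, a useful strategy would look weaker than it is.

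**Working it through.** **Step 1: does the text connect?** No figure in the protocol bears on this, so the first check sets the sections side by side.

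- Items of outcome 1: set by group agreement (Effect evaluation, item 1).
- Direction of success: set by the same agreement (effect research question 1).
- Agreement open to change: yes, at each new topic cycle (Intervention).
- New data on the same volumes reach the groups during the intervention: foreseen (Time schedule; Discussion). Feedback and outcome volumes come from the same two databases (Extraction of feedback data).
- Earlier topic reopened: yes (Table 3).
- Rule that the first agreement defines outcome 1: none stated. Targets are recorded after every session, so several versions may exist.

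Timing makes exposure possible but not certain. Measurement runs to 18 months and each group covers three topics. If these were spread evenly, which the protocol does not require, a cycle would last 18 / 3 = 6 months, the same as the data refresh. Groups that move faster could revise before any new data exist.

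**Step 2: how large could the effect be?** The inputs below are assumptions, because the protocol gives none of them. Let z be the standardised interim change of a target in the agreed direction and y its final change, both standard normal under no effect, with correlation ρ. Suppose half of the targets with z < 0 are dropped.

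- Fraction kept: 0.5 + 0.5 × 0.5 = 0.75.
- Mean of z among those kept: (0.3989 − 0.5 × 0.3989) / 0.75 = 0.266.
- Mean of y among those kept: ρ × 0.266, which is 0.133 SD at ρ = 0.5 and 0.186 SD at ρ = 0.7.
- Share of kept targets ending in the agreed direction, using P(y > 0, z > 0) = 1/4 + arcsin(ρ)/(2π):
  - ρ = 0.5: (0.3333 + 0.5 × 0.1667) / 0.75 = 55.6%.
  - ρ = 0.7: (0.3734 + 0.5 × 0.1266) / 0.75 = 58.2%.
  - With no selection: 50%.

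**Step 3: how sensitive is that to the assumed rule?** Suppose instead that the worst fraction f at the interim reading is dropped. The shift is then ρ × φ(z_f) / (1 − f), where z_f is the f-quantile of the standard normal:

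| ρ | f = 10% | f = 25% | f = 50% |
|---|---|---|---|
| 0.3 | 0.06 SD | 0.13 SD | 0.24 SD |
| 0.5 | 0.10 SD | 0.21 SD | 0.40 SD |
| 0.7 | 0.14 SD | 0.30 SD | 0.56 SD |

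**Step 4: can the sign reverse?** Yes. By symmetry, if half of the targets with z > 0 were retired as achieved, the shift would be −0.133 SD at ρ = 0.5 and −0.186 SD at ρ = 0.7.

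The protocol gives no SD for the change in a target, so these shifts cannot be turned into percentage points without a further assumption.

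**The case against.** The case against has real weight, and five parts of it need an answer.

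- **The Discussion expects reflection, not revision.** The sentence that permits revision does not mention follow-up data. Revision in response to follow-up data is an inference from several sections. This stands, and the point is worded accordingly: the text permits that sequence and makes it foreseeable, but does not prescribe it.
- **Revision may simply mean settling the agreement.** The sentence after the one on revision says that the agreements are then prepared for dissemination in the practices. That reading is fair. But a version settled at the next cycle can still postdate new data, so the gap stays open.
- **A withdrawn target may still count.** A reader might infer that failing targets will be dropped and so leave the endpoint. The documents do not say this. An item that a group once agreed to change still fits the wording "for which the group has agreed that change, either decrease or increase, would be necessary", and the session records keep every version. This stands.
- **The version to be analysed belongs in the analysis plan.** That is partly right, and such a plan may exist. The protocol has nevertheless defined the outcome through an instrument that it allows participants to rewrite. That is a weakness in the definition, not merely a missing detail.
- **Upward bias is not established.** A reader might also infer that the result must be inflated. Groups working in improvement cycles could as well retire met targets or tighten others, which would push the other way. This stands.

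Two safeguards in the Analysis section do not help. Blinding the analyst does not stop groups from changing the items, and intention-to-treat protects the randomised units, not the list of targets.

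**Conclusion.** The concern holds in limited form. The items and direction of outcome 1 come from agreements that may be revised at the next cycle, possibly after new data on the same volumes have been returned. The outcome can therefore depend on follow-up results and bias the before-after answer to effect question 1. Upward bias is plausible if failing targets are dropped or reversed, but neither sign nor size can be derived from the documents. The 0.13 to 0.19 SD figure is an illustration that rests wholly on the assumed drop rate and correlation; the other dropping rule gives 0.06 to 0.56 SD, and retiring met targets gives a negative shift.

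The reach is confined to outcome 1. Outcomes 2 and 3 are total volumes and inter-physician variation for the chosen topics, whose tests and drugs were predefined by the project group (Clinical topics). Revising an agreement does not change what they measure, so the between-arm comparison in effect question 2 is not touched. The change is still worth making because it is nearly free.

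**What to change.** Add a short statement to the outcome definition:

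- Outcome 1 consists of the items and direction recorded at the first test session and the first drug session on each topic.
- All of these stay in the analysis whatever the group revises later.
- Later revisions, additions and withdrawals are reported as process data.

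No new data collection is needed, because targets are already recorded after each session. Groups remain free to revise what they do in practice, so the pragmatic character of the trial is kept. The small cost is that some targets a group later judges unsuitable remain in the outcome. The rule should be in place before groups receive follow-up feedback.

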### Clinical topics

The set of clinical topics the GP groups can choose from in the main study has been proposed by the authors. After eligible topics were selected and divided over the two trial arms, both arms were balanced in terms of the weight of the topics. The weight depends on the prevalence of the underlying disease and whether the emphasis within the topic is on either the volume of tests ordered or the drugs prescribed. The two sets of topics are also balanced in terms of subjects, emphasising diagnostic or prescribing features (Table 1). Each topic includes a number of tests [See Additional file 2] and drugs [See Additional file 3] predefined by the project group. For the purpose of feedback and education, these include both well-accepted and commonly not accepted (or even obsolete) tests and drugs. Educational materials on each topic will be based on the relevant national primary care guidelines from the Dutch College of General Practitioners, guidelines from the Dutch Institute for Healthcare Improvement (CBO), and international guidelines if applicable. Guidelines will be read and 'condensed' into short versions called modules. These modules have been drafted by one of the authors (JT) and then commented on by an expert on the topic. Indicative prices for each test and drug will be provided, as well as a short description of its values and drawbacks, given the indication. Each module will consist of a maximum of six easily searchable pages.

### Extraction of feedback data

Data on test ordering behaviour will be extracted by the regional coordinators from the various databases available at the participating hospital laboratories or primary care diagnostic centres. Each centre will receive a data fact sheet prescribing the required data format. This format is based on rational criteria for laboratory test registration to facilitate the integration of the individual databases into one main database. All datasets on diagnostics will be combined into one newly formed database, to be maintained by UM (Figure 2). Data on prescribing behaviour will be extracted from the databases of health insurers and collected into one database, as has already been done at our institute. This database consists of the reimbursements for prescriptions written by GPs for approximately 5.5 million persons in the south of the Netherlands. Feedback will then be derived from the two main databases and processed into graphical comparative feedback reports. Data will be presented as the volume of tests ordered (*e.g*., haemoglobin) or defined daily dosages (DDDs) prescribed per 1000 patients per six months. Participating GPs will receive their data as clustered column charts, each cluster presenting the data for the individual GP, the practice in which he or she works, the small group and the wider region. An example of such a graphical feedback report is shown in Figure 3.

**Figure 2 F2:**
[figure not shown]
**Data and Knowledge flowchart**.

**Figure 3 F3:**
[figure not shown]
**Example of a graphical comparative feedback sheet**.

### LQIC meeting structure

Each meeting will be structured according to a uniform schedule. After participants have studied the feedback in pairs or as a group, they will discuss it. Subsequently, the guidelines as described in the educational materials will be discussed in relation to the feedback. A plan will then be formulated to improve the test ordering or prescribing behaviour. The next step will involve addressing and discussing all the barriers to change at individual and group levels. Finally, working agreements will be created regarding test ordering and prescribing behaviour for the tests and drugs discussed. A standardized group meeting structure card will be provided to each LQIC, showing the structure as recommended by the researchers. However, groups will be free to adapt the structure to their own preferences or needs.

### Training

The participating medical coordinators and local community pharmacists will be trained prior to the first LQIC session, in a two- to three-hour standardized training session covering three main subjects. The first subject will involve an explanation of the structure of the trial, the objectives, the development of the outlines, the source of the feedback data, and the process of data gathering. The second subject will be the preferred structure for the meetings, the tools that are to be used, how to read the feedback reports and relate the feedback to the guidelines. The final subject of the training session will be how to act as a moderator instead of a chair during a meeting. Training sessions will partially be constructed like a LQIC meeting, with the trainees acting as GPs and the trainer as the moderator.

